### Design

A mixed-method research design will be carried out. Three different study designs will be used:

***Phase 1.*** Prospective longitudinal study in two steps:

A first step of 18 months, in which a first intervention of audits and seminars in healthcare professionals will be carried out, focused on an effective and efficient registry of hospital falls in older people. This first phase is crucial to identify temporal patterns of falls in relation to specific intrinsic and extrinsic risk factors among hospitalized older people, as well as the levels of fatigue/sleepiness, attention and cognitive functionality of the healthcare professionals who attend to an in-hospital fall.A second step of application of a multidimensional prevention programme for 15 months focused on organizational, educational and behavioural elements applied to admitted older people and healthcare professionals.

***Phase 2.*** Retrospective study of the fall records found in the institutional databases of the study centres in the period between January 2018 and September 2020. This period covers the first (January 2018–May 2019) and second phases (June 2019–September 2020) of the project, as previously indicated.

***Phase 3.*** Descriptive exploratory study with a qualitative approach, focus groups made up of healthcare professionals: doctors, nurses and nursing assistants who provide and have provided their professional services in the field of study, in the periods in which the longitudinal and retrospective studies have been carried out.

### Participants and setting

***Phase 1.*** The study subjects will be all those patients over 65 years of age who suffer one/several fall(s) during their admission to the Reina Sofia University Hospital in Córdoba and in the three regional hospitals of the Province of Córdoba (Cabra, Montilla and Pozoblanco) from January 2018 to September 2020.

Specifically, for the study of the levels of fatigue/sleepiness, attention and cognitive functionality of the healthcare professionals, the reference nurses of the older person who has an in-hospital fall during the study period will also be included.

***Phase 2.*** Institutional records of falls occurring in patients over 65 years old. In order to contrast with the prospective design, the institutional records of the four hospitals will be collected during the same period (January 2018 to September 2020).

***Phase 3.*** Healthcare professionals (doctors, nurses and nursing assistants) will be interviewed.

### Inclusion and exclusion criteria

***Phase 1.*** Regarding patients, they should have been admitted in the aforementioned hospitals, should be over 65 years old and suffer an in-hospital fall. Furthermore, they should sign an informed consent accepting to participate in the study.

Healthcare professionals should have the following requirements: to sign an informed consent accepting to take part in the study and to be nurses in charge of the care of older people suffering from hospital falls, despite not witnessing the event.

Patients who suffer from hospital falls and healthcare professionals who take care of them will be included in the study continuously, which means after every single fall event.

In both cases (patients and healthcare professionals), the sampling will be total.

***Phase 2.*** Records of falls suffered in patients over 65 years old collected in different institutional databases (adverse event report, clinical record of the patient…) in the four hospitals. As in phase 1, the sampling will be total.

***Phase 3.*** Selection of healthcare professionals will be intentional and with the leverage of the collaboration with the centres involved. One person for each sector (doctors, nurses and nursing assistants). Inclusion criteria will be: (i) healthcare professional who has worked in the four hospitals during the time the longitudinal study is carried on; (ii) professionals of clinical units where hospital falls will be recorded during the longitudinal study; and (iii) professionals of clinical units in that are important to the risk of in-hospital falls, by pathologies, dependence, motor or mobility disorder, etc.

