## Methods/design

### Aims

The main aim of this study will measure the effect of the implementation of a falls prevention programme based on temporal patterns and relative risks factors.

Secondary aims will be: (i) to identify temporal patterns in the incidence of hospital falls and intrinsic and external risks factors, pre- and post-intervention; (ii) to establish differences in temporal patterns according to the hospital setting (teaching or non-teaching) and the different types of wards (medical, surgical or mixed), pre- and post-intervention; (iii) to study the role of circadian time in drug administration for older people suffering from hospital falls, pre- and post-intervention; (iv) to identify the level of fatigue/sleepiness, attention and cognitive functionality of healthcare professionals intervening during hospital falls, pre- and post-intervention; and (v) to develop a uniform, simple and intuitive method to record hospital falls in order to improve the effectiveness of the registration of falls and to assess the implementation pre- and post-intervention.

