### Study variables

The main dependent variable will be the number of hospital falls. A hospital fall will be defined as “the consequence of a non-intentional and sudden movement towards the floor from a more elevated position” in hospital settings.

Other independent variables related with the patient who experiences a hospital fall include: (i) sociodemographic and economic data (age, gender, marital status and level of education); (ii) time (hour and minute, day and shift work) of fall; (iii) patient position (from the bed with or without bedrails, sitting, walking, and so on) and witness of the fall (roommate, family member, healthcare professional or no witness); (iv) use/no use of footwear and kind (open or closed); (v) cause of fall (instability (general instability and balance loss), dizziness (syncope, fainting and cardiovascular accident), drug adverse effects (diuretics, anti-hypertension and other drugs), accident (event with no identifiable cause), ambient-related (dropped objects, obstacles and wet floor), fragility (extreme fragility or weakness) or others); (vi) location of the fall (hospital room, bathroom, corridor, public area or others); (vii) fall-related injuries and severity (no wound/no consequences, minor wounds (grazes and minor contusions), afflicting wounds (contusions requiring stitches, fractures and skull trauma) or others (not afflicting wounds but still in need of minor medical intervention)); (viii) number and kind of coexisting clinical conditions; (ix) prescribed drugs and their time of administration; (x) chronotype measured by the Horne-Östberg Questionnaire (1976); (xi) quality of life in terms of body functionality, physical limitations, body pain, social role or function, mental health, emotional limitations, vitality, energy or fatigue and general perception about own health; and (xii) general health status in terms of somatic symptoms, anxiety, insomnia, social dysfunction and depressive symptoms.

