### Data analysis

***Phases 1 and 2.*** For the analysis of quantitative data, descriptive statistics will be used, including measures of frequency, central tendency and dispersion according to the type of variable (quantitative or qualitative). Normality will be calculated with Shapiro-Wilk’s test and homogeneity with Levene’s test. To compare proportions of categorical variables, the chi-square test for contingency tables will be used. In the case of 2 × 2 tables, such tests with Yates correction will be used, and if the expected frequency is ≤ 5, Fisher’s exact test will be used. To compare mean values between the quantitative variables of two groups, Student’s t test for independent samples will be used. For the comparison of the mean values between quantitative variables and hospitals, the one-factor ANOVA test and ad-hoc tests with correction by GT2 Hochberg (if variance is homogeneous) or Games Howell (if variance is unequal) will be used. For the correlation between the quantitative variables, Pearson’s correlation coefficient will be used. For the logistic regression, multivariate analysis will be used.

All hypothesis tests will be bilateral. All tests with a confidence level of 95 % (p < 0.05) will be considered statistically significant.

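### Phases 1 and 2 contain only falls, so the plan cannot estimate how a patient, drug or nurse factor changes the risk of falling, although it states that purpose

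*Protocol article*

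**What the plan says.** **Who is observed.** In the Protocol article, under Participants and setting, the Phase 1 subjects are "all those patients over 65 years of age who suffer one/several fall(s) during their admission". The Inclusion and exclusion criteria require that a patient "should be over 65 years old and suffer an in-hospital fall". They add that patients and the professionals caring for them "will be included in the study continuously, which means after every single fall event". Data collection: Procedure confirms that the fatigue, attention and cognitive measures are obtained only in professionals linked to a fall. Phase 2 is defined as "Records of falls suffered in patients over 65 years old collected in different institutional databases".

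**What is recorded.** Study variables names the number of falls as the main dependent variable. It lists patient and nurse factors as independent variables, among them "prescribed drugs and their time of administration".

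**What the data are for.** The first step of Phase 1 is meant to "identify temporal patterns of falls in relation to specific intrinsic and extrinsic risk factors among hospitalized older people". Aim (iii) is "to study the role of circadian time in drug administration for older people suffering from hospital falls", and the sentence goes on to specify a comparison before and after the intervention. The Background subsection on temporal patterns asks whether the hour at which a drug is given influences whether falls occur. The subsection on chronoprevention wants staff variables evaluated so that the aetiology of falls can be defined. Study variables (Step 2) says the programme will be adjusted to temporal patterns and to risk factors. The Discussion wants nurse chronotype, sleep quality and health related to patient safety.

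**What analysis is named.** Data analysis lists group comparisons, correlation and Cosinor analysis, and says "For the logistic regression, multivariate analysis will be used". It names no outcome for the logistic model.

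**The concern.** A fall is the entry condition for every patient and, through the patient, for every nurse. Drugs, comorbidity, chronotype and nurse sleepiness are therefore recorded only where a fall has happened. Their frequency among falls mixes two things: how much the factor raises the risk, and how common it is among older inpatients or among shifts in general. The plan describes no source that would separate them.

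The labels invite the wrong reading. With falls called dependent and the factors called independent, a factor often seen at falls is easily reported as a cause. The plan intends to act on the result: the measures follow analysis of the first 18 months of falls, and the Discussion foresees clinical practice guidelines. The Limitations section discusses unwitnessed falls, reliance on staff reporting and the lack of a clinical trial, but not the absence of a non-fall comparator.

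**Working it through.** The document gives no sample size, event count, rate or effect size on this point, so there is no figure to reproduce. The check asks what fall-only data can identify. **All numerical inputs below are assumed.**

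**1. Main effect of a factor on falling.** Let *p* be the exposure prevalence among fallers (observed) and *q* the prevalence among non-fallers (not collected).

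OR = [p/(1−p)] / [q/(1−q)]

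With p = 0.40 the case odds are 0.40/0.60 = 0.667.

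| q | odds in non-fallers | OR for falling |
|---|---|---|
| 0.20 | 0.250 | 2.67 |
| 0.30 | 0.429 | 1.56 |
| 0.40 | 0.667 | 1.00 |
| 0.50 | 1.000 | 0.67 |
| 0.60 | 1.500 | 0.44 |

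The same faller data fit harm, no effect and protection.

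**2. Logistic model of period (after v before) on a factor, among fallers.** Let RR be the factor's true rate ratio for falling, and q₁ and q₂ its prevalence among patients at risk before and after.

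OR = [q₂·RR/(1−q₂)] / [q₁·RR/(1−q₁)] = [q₂/(1−q₂)] / [q₁/(1−q₁)]

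If RR is the same in both periods it cancels.
- q₁ = q₂ = 0.40: OR = 1.0 for RR = 1 and for RR = 3.
- q₁ = 0.40, q₂ = 0.50: OR = 1.000/0.667 = 1.5 for RR = 1 and for RR = 3.

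The model can be fitted, but it does not estimate the factor's effect on falling.

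**3. Factor by time of day, among fallers.** Let the factor's rate ratio be 3.0 in the morning and 1.5 otherwise, with prevalence q constant over the day.

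Case-only OR = [q·3.0/(1−q)] / [q·1.5/(1−q)] = 3.0/1.5 = 2.0

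The result is 2.0 for q = 0.20, 0.40 and 0.60, and equals the true ratio of rate ratios. The unknown q cancels, so this contrast is estimable.

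**4. What step 3 depends on.** Suppose the true ratio of rate ratios is 1, but prevalence among patients at risk is 0.40 in the morning and 0.20 otherwise. The case-only OR is then (0.40/0.60)/(0.20/0.80) = 0.667/0.250 = 2.67, with no real difference. The assumption is reasonable for factors fixed over an admission, such as comorbidity, chronotype or having a drug prescribed. It is doubtful for exposures that follow the clock, such as a recent dose or a nurse's state on night shift.

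**The case against.** A reader might infer that the study has no comparison group at all and that its data say nothing about falling. The document does not support that. All the secondary aims specify a comparison before and after the intervention, and aim (ii) adds hospital setting and ward type. Step 3 shows that differences in time-of-day pattern between factor groups, which are the study's own subject, can be estimated from fallers under a stated assumption.

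A reader might also infer that the logistic regression is invalid. Its outcome is merely unnamed, which is detail that an analysis plan or full protocol may supply. Injury severity, witness and location all vary among falls and could be modelled.

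The defence can add three points. Aim (iii) is confined to patients who fell, and aim (iv) asks only for a level, so neither promises an odds ratio for falling. The main aim rests on the number of falls and is not affected. The listed measures do not hang on a drug-timing estimate: the only drug item is a poster encouraging medication review.

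All of this stands and limits the reach of the point. It does not remove it. The purpose of explaining falls is stated in the Background, in Study variables and in the Discussion. An analysis plan can name an outcome, but it cannot supply patients or shifts without a fall.

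**Conclusion.** The point holds in this form: Phases 1 and 2 have no non-fall comparator, so the main effect of a patient, drug or nurse factor on the risk of falling is not identifiable, and the text states purposes that need it. Under the assumed inputs the same data are compatible with odds ratios from 2.67 to 0.44. That conclusion follows from the eligibility rules and does not depend on the numbers chosen.

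Comparisons among falls (before v after, hospital, ward, injury v no injury) remain estimable. So do factor-by-time-of-day contrasts, if the factor's prevalence among patients at risk is constant over the day. The secondary aims and the interpretation are concerned, not the main aim. The change is worth making because it is cheap and prevents frequency among falls from being read as risk.

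**What to change.** 1. In Data analysis, restrict the logistic models to outcomes that vary among falls, such as injury v no injury.
2. For risk factors and drug timing (aims (i) and (iii)), test factor-by-time-of-day contrasts among falls. State the constant-prevalence assumption and say for which factors it is credible.
3. Report patient, drug and nurse factors as characteristics of falls and of their timing, not as risk factors for or causes of falling. Reword the chronoprevention subsection of the Background, Step 2 in Study variables and the Discussion to match. Add the missing non-fall comparator to the Limitations.

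**Optional.** A self-controlled analysis of dose times (conditional logistic regression within patient) could address short-lived drug effects, but only if administration times for earlier days of the same admission are available. The document does not show that they are. Its limits must be stated. Scheduled drugs are given at similar hours each day, so windows at the same clock time yield few discordant pairs. Windows at other hours are confounded by daily care activity, such as the bathing-related morning peak noted in the Background.

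**Cost.** Items 1 to 3 need analysis wording only and no new data. The price is that the study gives up claims about what causes falls.

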### Data collection: Procedure

***Phase 1***: The project will be explained to the institutional managers of the centres included in the study, who will appoint a coordinator to ensure proper development and will work in coordination with the research team. In these meetings, the process of recording falls will be disclosed, as well as the other variables.

Prior to data collection, meetings will be held with those responsible for the Clinical Management Units and special mention will be made of the areas that are expected to have a greater number of events (internal medicine, neurology, trauma, rehabilitation, …). Additionally, the dynamics of data collection will be explained.

On the other hand, being focused more on healthcare professionals (especially nurses) from the different study centres, several seminars will be held (first intervention), explaining how data collection should be done, as well as the definition of variables included in the record sheet. Such seminars will be proportional to the number of workers in the different centres included, being distributed over different days so that the number of workers receiving information is as large as possible. In addition, specific audits will also be carried out in each Clinical Management Unit.

During the first 18 months of study development, each time a fall occurs, in addition to recording the circumstances of the fall, it is necessary to obtain the informed consent of the patient to know their quality of life, general functional status, sleep pattern and chronotype. In healthcare professionals, informed consent must also be obtained to know the previous variables, as well as the values of fatigue/sleepiness, attention and cognitive functionality. In this sense, as it has been commented on in the inclusion/exclusion criteria, these variables will only be known in the healthcare professionals responsible for the older person, who have visualized and/or attended the fall event, even though the fall may be the result of a collective lack of attention from all the staff and not from a single person.

Once the prospective data collection period has started (January 2018), monthly individualized audits will be carried out in the different Clinical Management Units, aimed at managing correct data collection. Furthermore, these audits will allow obtaining a perspective of the fall event in relation to the number and related circumstances.

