### Limitations

In the quantitative phases, the non-visualization of the fall may suppose an uncertain record of the event and its circumstances. Furthermore, both the record of falls and the section related to the state of health of the professionals are circumscribed to the idiosyncrasy of healthcare professionals. Limitations that are also present in the retrospective phase. A clinical trial could have more generalizability of the results and less bias. However, it should be noted that the interventions are established based on temporal patterns of incident events and relative risk factors for falls and related injuries in the participating hospitals. Therefore, with the intention of improving patient safety, the intervention is tailored to the casuistry of each centre.

The data obtained in the qualitative phase are subjective to perceptions of healthcare professionals. They cannot always express their opinions [40].

An information sheet on the study will be delivered to both the patient and the participating professionals, for which they will need to sign the informed consent.

For the retrospective study, the data will be delivered to the Principal Investigator anonymized.

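### Signed consent, sought after the fall, is a Phase 1 inclusion criterion; read literally it removes non-consenting fallers from the main fall count and contradicts the total sampling stated elsewhere

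*Protocol article*

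**What the plan says.** All references are to the protocol article.

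- *Inclusion and exclusion criteria*, Phase 1: after admission, age over 65 and an in-hospital fall, a further condition for patients is added: "Furthermore, they should sign an informed consent accepting to participate in the study". No time limit is attached.
- Same section, on timing: patients and professionals "will be included in the study continuously, which means after every single fall event". Consent is therefore sought once the outcome event has happened.
- Same section, on sampling: "In both cases (patients and healthcare professionals), the sampling will be total".
- *Participants and setting*, Phase 1: "The study subjects will be all those patients over 65 years of age who suffer one/several fall(s) during their admission". There is no consent condition here.
- *Study variables*: "The main dependent variable will be the number of hospital falls", again with no consent condition.
- *Data collection: Procedure*, Phase 1: "in addition to recording the circumstances of the fall, it is necessary to obtain the informed consent of the patient to know their quality", followed by the other questionnaire variables (functional status, sleep and chronotype). Here consent is a separate act from recording the fall.
- *Limitations*: an information sheet goes to patients and professionals, "for which they will need to sign the informed consent". What happens to the falls of those who do not sign is not stated.
- Phase 2 takes institutional fall records from the same four hospitals over the same period. They are delivered anonymized, with no consent criterion stated.

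**The concern.** The main aim is to measure the effect of the prevention programme, and the main outcome is a count of falls before and after it. If signing a form after the fall decides whether the fall is counted, the recorded number is the product of two quantities: how many falls occurred and what share of fallers signed. A change in that share between the periods would look like a programme effect or hide one.

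The time patterns are exposed as well. The programme is to be built on Cosinor curves fitted to the falls of the first period. The article's own categories for cause and injury include syncope, extreme weakness, fractures and skull trauma. It is a reasonable inference, though not documented, that such patients are less able to sign soon after a fall. If signing varies with severity or hour of day, the injury profile and the clock-time curves are observed selectively, even when the overall consent rate is the same in both periods.

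**Working it through.** **Step 1: which falls enter the count?** The statements divide as follows.

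| Place in the article | Consequence for a faller who does not sign |
|---|---|
| Inclusion and exclusion criteria, consent sentence | Not included |
| Limitations, consent restated | Signature needed; fate of the fall record not stated |
| Inclusion and exclusion criteria, sampling sentence | Included (sampling is total) |
| Participants and setting | Included (all fallers over 65) |
| Data collection: Procedure | Fall recorded; questionnaires missing |
| Study variables | Outcome defined without a consent condition |

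The eligibility sentence and the sampling sentence cannot both govern the count. The article does not say whether the main count comes from the sheets of consenting patients, from all Phase 1 sheets or from Phase 2.

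**Step 2: size of the distortion if the eligibility sentence governs.** The article gives no consent rate, expected fall count, effect size or power, so there is no stated figure to reproduce. Let c1 and c2 be the consent proportions before and after the programme.

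Observed post/pre ratio = true ratio × (c2 / c1)

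All consent rates below are assumed.

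| c1 to c2 | c2/c1 | Observed, true ratio 1.00 | Observed, true ratio 0.80 |
|---|---|---|---|
| 90% to 90% | 1.00 | 1.00 | 0.80 |
| 60% to 60% | 1.00 | 1.00 | 0.80 |
| 80% to 70% | 0.875 | 0.875 | 0.70 |
| 70% to 80% | 1.143 | 1.14 | 0.91 |
| 80% to 60% | 0.75 | 0.75 | 0.60 |
| 60% to 80% | 1.333 | 1.33 | 1.07 |

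With stable consent the ratio is right, although each count is too low. When consent shifts, the ratio errs by exactly the consent ratio.

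**Step 3: chance of a false finding.** Assume N falls in each period, equal exposure, no true change, and a two-sided 0.05 Wald test on the log ratio of two Poisson counts. Equal exposure is a simplification, since the two steps are described as 18 and 15 months.

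SE = √(1/(N·c1) + 1/(N·c2)); z = |ln(c2/c1)| / SE

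For N = 200 and 80% to 70%: SE = √(1/160 + 1/140) = 0.116, |ln 0.875| = 0.134 and z = 1.15, so the probability of a significant result is about 21%.

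| N per period (assumed) | 80% to 80% | 80% to 70% | 80% to 60% |
|---|---|---|---|
| 100 | 5% | 13% | 39% |
| 200 | 5% | 21% | 66% |
| 400 | 5% | 37% | 92% |

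**Step 4: patterns at stable consent.** The same multiplication applies within a period. If, by assumption, 60% of night fallers and 80% of day fallers sign in both periods, the observed night/day ratio is 0.60/0.80 = 0.75 of the true one. The post/pre ratio at each time of day is untouched, but the curve used to time the preventive measures is distorted.

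**The case against.** The strongest reply is that no omission is established. The outcome definition carries no consent condition, the population is all fallers over 65, sampling is total, and the fall sheet is completed by the referring nurse rather than the patient. The procedure section can be read as the arrangement recommended here: record every fall, and ask consent for the questionnaires. This stands to the extent that exclusion of non-signers follows only from the literal eligibility rule. It does not remove the contradiction, because that rule asks for consent to take part in the study, and staff in four hospitals could apply either reading.

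Phase 2 is a second safeguard, since a shortfall caused by consent might show against institutional records. This stands in part. Phase 2 is planned as a comparison with the prospective study and is not named as the source of the main count. The sections on registration culture and Discussion themselves report poor registration and underestimation of falls.

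Third, consent rates and refusal patterns are assumed, and arrangements for patients unable to sign may be in the full protocol. That is right, and the figures are illustrations only.

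Two stronger readings should not be drawn:

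- A reader might infer that the count follows consent rather than falls. It would follow falls multiplied by consent, and a stable rate leaves the ratio unbiased.
- Because the procedure text opens with "During the first 18 months of study development, each time a fall occurs, in addition to recording the circumstances of the fall", a reader might infer a filter in the first period only, which at 80% consent would inflate the post/pre ratio to 1/0.80 = 1.25. This joins two incompatible readings. The eligibility rule has no time limit, so if it governs, both periods are filtered. If the procedure text governs, consent concerns the questionnaires and nothing is filtered.

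**Conclusion.** The point holds as a contradiction in the stated text with a conditional bias. It is firm that signed consent, sought after the fall, is a Phase 1 inclusion criterion, and that this conflicts with total sampling, the all-fallers population and the procedure section. It is conditional that non-signers' falls are missing from the main count and the Cosinor input: this depends on the eligibility rule being applied as written.

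On that condition, the error in the post/pre ratio equals the consent ratio. It is zero if consent is stable, and about 12 to 14% for a shift of ten percentage points between 70% and 80%, under assumed rates. Selective observation of severity and clock time can remain at stable consent; its size cannot be derived from the article. The change should be made, because it removes a possible bias from the main comparison at little cost.

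**What to change.** Reconcile the sections with four statements:

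1. Every recorded fall in a patient over 65 enters the main count and the Cosinor analyses in both periods, whatever the consent status, using de-identified fall sheets.
2. The consent criterion applies only to the patient and nurse questionnaires.
3. The source of the main count is named (all Phase 1 fall sheets, or Phase 2 records), with the other source used as the comparison.
4. The proportion consenting is reported by period, hospital and injury severity, so that selection in the questionnaire data can be judged.

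The cost is wording plus confirmation from the ethics committee that de-identified fall sheets may be counted without individual consent. The approval itself is not shown, so this cannot be taken for granted, but Phase 2 already plans to use anonymized fall records from the same hospitals and period with no stated consent criterion. Essentially no new data collection is needed. If confirmation were refused, the article should say that the main count covers consenting patients only, and the consent proportions by period would be needed to interpret the comparison.
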